## **9.6 Quality Control**

Oversight of the study is the responsibility of AbbVie.

The sites will be instructed in the protocol regarding the use of the questionnaires, the functionality and handling of the eCRF, and the requirements to maintain source documents for each patient in the study in order to ensure that all patient questionnaires will be completed by patients.

Different quality assurance methods will be implemented to ensure integrity of the information reported over the course of the project. All data will be entered via eCRF. The eCRFs will be submitted to be entered into the electronic database maintained by external data management provider.

After data entry, computer logic checks will be run to check for inconsistent data. Any necessary corrections will be made to the database and documented via queries, source data clarification forms and an audit trail regarding all changes will be available. A manual review of selected line listings will also be performed at the end of the study.

## **9.7 Limitations of the Research Methods**

Results cannot be generalized to the whole RA patient population universe due to enrolment of sub optimally controlled patients.

Results must be carefully interpreted due to the observational and cross-sectional nature of the study. Information about the percentage of screened patients that agreed to participate in this study will be not collected which may result in selection bias.

No hypothesis testing will be performed in the primary analysis. All other statistical tests performed in secondary analysis will be performed without formal hypothesis testing and resulting p-values will be interpreted in a descriptive manner.

Factors associated to cultural differences may influence the results per countries. Country specific sub analyses should be interpreted carefully due to low sample size.

There is a potential imbalance in the size in subgroups per treatment used or per presence of comorbidities. Comparisons between different subgroups should be interpreted in exploratory manner only. Confounding factors (e.g., disease duration and severity, level of treatment response, and number and type of co-morbidities) may not be equally distributed between the groups, which can lead to bias and subsequent misinterpretation.

No validated questionnaires will be used for assessing needs for PSP, treatment preferences and expectations. Adherence results will be based on self-reported outcomes that may be influenced by self-presentational and recall biases. Patients may overestimate the extent of their adherence. Past HRU is based on patient interviews in addition to patient charts, similarly might result in recall-biases.

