### Patient Selection Criteria

Patient attending a routine visit, who fulfill ALL the following selection criteria, can be included:

- Male or female.
- Adult (aged  $\geq 18$  years).
- Has rheumatoid arthritis (RA), diagnosed either by the 1987-revised ACR classification criteria or by the 2010 ACR / EULAR classification criteria for RA.
- Currently treated with any kind of approved csDMARDs, tsDMARDs or bDMARDs.
- Has been exposed to no more than 2 bDMARDs at the time of the enrollment.
- His/her RA is sub optimally controlled, despite full tolerable dose of current DMARD therapy administered for  $\geq 3$  months.

- Definition of suboptimal disease control: having high or moderate disease activity (as defined by having DAS28 > 3.2) for at least 1 month but not more than for 4 months prior to the enrollment.
- Understands the language and willing/able to complete the patient reported outcome questionnaires.
- Does not participate in any kind of clinical study for RA.
- Has provided written authorization to the investigator to use and/or disclose personal and/or health data, or informed consent if requested by the local regulations.

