### **9.3 Study Size**

Approximately 1500 RA patients will be included in the study. The study will include 100 sites in approximately 20 countries in Europe, America and Asia. Countries will recruit between 30 and 200 patients per country depending on the available patient population.

Current sample size calculation is based on information of global satisfaction measured by TSQM 1.4. It is also assumed that similar number of patients will be allocated to each country so that country level analyses will be explored, as well as overall population. Based on the literature [51, 83], it seems reasonable to assume that the standard deviation for the global satisfaction is about 20 with mean value range from 71 – 91.

A given sample size of N=1500 will be able to provide a 95% confidence interval (CI) with a half width of 1.01 in the overall study population.

For country specific analysis a sample of N=50 will be able to provide a 95% confidence interval (CI) with a half width of 5.68. . For country specific analysis a sample of N=30 – 200 will be able to provide a 95% confidence interval (CI) with a half width of 7.47 to 2.79.

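### No rule says which eligible patients are invited and participation is not counted, so selection bias in the primary satisfaction mean is neither limited nor assessable

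*Protocol*

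**What the plan says.** The only recruitment rule is in Protocol section 9.0, Patient Selection Criteria: "Patient attending a routine visit, who fulfill ALL the following selection criteria, can be included". The list that follows defines eligibility. Neither it nor any other section says whether eligible patients are approached consecutively, at random, by quota or otherwise, and no screening log is described.

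Section 9.7 then settles the matter of participation data: "Information about the percentage of screened patients that agreed to participate in this study will be not collected which may result in selection bias". The data list in section 8.1 covers enrolled patients only, and section 9.4 limits what reaches the sponsor to data named in the protocol.

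On precision, section 9.3 states: "A given sample size of N=1500 will be able to provide a 95% confidence interval (CI) with a half width of 1.01". It assumes that "the standard deviation for the global satisfaction is about 20 with mean value range from 71 – 91". For single countries it says that "a sample of N=30 – 200 will be able to provide a 95% confidence interval (CI) with a half width of 7.47 to 2.79". Section 9.5.1 makes the satisfaction score in the full study population the primary endpoint.

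**The concern.** The primary result is one mean, estimated without a randomised contrast that could cancel selection. Its meaning depends on how the enrolled patients relate to all patients with suboptimally controlled RA at these clinics. Two safeguards are usual: an invitation rule that limits choice, and a participation count that shows how much choice or refusal took place. The protocol has neither. A later statistical analysis plan cannot repair this, because data that were never collected cannot be recovered.

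A link between taking part and satisfaction is plausible. The instruments whose length the protocol gives add up to 20 (HAQ) + 13 (FACIT-F) + 14 (TSQM) + 36 (SF-36) + 17 + 6 + 11 (Appendices 3 to 5) = 117 items, before WPAI, eHEALS and the visual scales. Completed questionnaires are transcribed into the eCRF (section 9.4), and the health care professional is asked to review them (section 11.1). Patients less content with treatment might decline more often or be asked less often. The documents do not establish that this happens, or in which direction.

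At stake is how the interval is read. A reader who sees a mean with a margin of about one point will take it as a precise description of the target population, when it carries no allowance for who was enrolled.

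**Working it through.** **Inputs from the protocol.** N = 1500, SD = 20, two-sided 95% confidence, country N from 30 to 200 (all section 9.3). The SD is given there for global satisfaction; I take it to apply to the primary score.

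**Inputs the protocol does not give.** r = share of eligible patients enrolled; D = difference in mean score between enrolled and non-enrolled eligible patients. Both are assumptions, shown as ranges.

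**Step 1: reproduce the stated precision.** Half-width = t(0.975, N−1) × SD/√N.
- N = 1500: SE = 20/√1500 = 0.516; half-width 1.013 (stated 1.01).
- N = 30: 7.468 (stated 7.47).
- N = 200: 2.789 (stated 2.79).

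The figures are right. The formula contains SD and N only, so it covers sampling error and nothing else.

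**Step 2: bias in the mean.** Bias = (1 − r) × D. Setting this equal to 1.013 gives D = 1.013/(1 − r).

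| Share enrolled r | D at which bias equals 1.013 | Bias if D = 3 | Bias if D = 5 | Bias if D = 10 |
|---|---|---|---|---|
| 0.90 | 10.13 | 0.3 | 0.5 | 1.0 |
| 0.80 | 5.06 | 0.6 | 1.0 | 2.0 |
| 0.70 | 3.38 | 0.9 | 1.5 | 3.0 |
| 0.60 | 2.53 | 1.2 | 2.0 | 4.0 |
| 0.50 | 2.03 | 1.5 | 2.5 | 5.0 |

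Against the SD of 20, a difference of 5 points is 0.25 SD and one of 2 points is 0.10 SD.

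**Step 3: effect on the interval.** With bias b, coverage of the nominal 95% interval is Φ(1.96 − b/SE) − Φ(−1.96 − b/SE), with SE = 0.516. This gives about 84% at b = 0.5, 51% at 1.0, 17% at 1.5 and 3% at 2.0. A larger N shrinks SE but leaves b unchanged.

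**Step 4: country level.** At N = 200, D would have to be 2.789/0.1 = 27.9 points at r = 0.90, 2.789/0.2 = 13.9 at r = 0.80, or 2.789/0.5 = 5.6 at r = 0.50. At N = 30 and r = 0.50 it would have to be 7.468/0.5 = 14.9. The comparison with stated precision therefore matters mainly for the overall mean.

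**The case against.** The strongest reply is that section 9.7 already discloses the problem. It names the missing participation figure and possible selection bias, and urges caution about the cross-sectional design, country results and subgroup comparisons. This stands: nothing is concealed or miscalculated. But disclosure neither limits the bias nor lets anyone judge its size.

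Four stronger readings are tempting, and the documents do not support them.

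- **That investigators pick whom to ask.** Saying that eligible patients may be included is ordinary eligibility wording. Discretion is an inference from the absence of an invitation rule.
- **That site numbers show room to choose.** 1500 patients at 100 sites is 15 per site on average over about nine months. The eligible pool per site is unknown, and the criteria are narrow: suboptimal control lasting one to four months, at most two biologics, and no other RA study. Fifteen could be most of a site's eligible patients or few of them.
- **That the bias does exceed 1.01.** Both inputs are assumed. At 90% enrolment a difference of about 10 points is needed. Nor does the protocol give a TSQM difference that would matter clinically, and 1.01 is a low bar because N is large.
- **That the study is purely descriptive.** Only its primary analysis is. Section 9.5.3 also plans subgroup tests, regression and predictive models.

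It is also fair to object that a count yields r but not D, and that a change late in enrolment covers little of it. The amendment is dated 18 March 2019 and collection is planned to end on 31 May 2019, 74 days later. Both objections stand and limit what the fix can deliver.

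**Conclusion.** The point holds as a gap in design, not as a demonstrated bias. The protocol sets no invitation rule and decides against collecting participation, so selection bias in the primary mean is neither limited nor assessable. The 1.01 is correct as sampling error and should not be read as total uncertainty.

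Whether the bias exceeds that margin depends on two unknowns. It does so at differences above about 10, 5 or 2 points for enrolment shares of 90%, 80% or 50%. The conclusion assumes SD 20 for the primary score and makes no claim about direction.

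Section 9.7 also misplaces the cause. Failing to count participation does not produce selection bias; it removes the means of judging it. This is a cheap improvement worth making, not an error that invalidates the primary analysis.

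**What to change.** 1. **Section 9.0, Patient Selection Criteria.** State that consecutive eligible patients at routine visits will be invited until the site's target is reached. The protocol gives country ranges but no site targets, so these need to be set.
2. **Section 9.7.** Replace the decision not to collect participation with an anonymous count at each site of patients eligible, invited and agreeing. All three are needed: an agreement rate alone misses eligible patients who were never asked. Add the count to the data listed in section 8.1, since section 9.4 admits only data the protocol specifies.
3. **Reporting.** Give the counts overall and by country beside the primary mean, with a bounding statement: (1 − observed r) × a stated range of D. For example, r = 0.80 with D between −10 and +10 gives ±2.0 points.
4. **Wording of section 9.7.** Say that without a count selection bias cannot be assessed, not that the missing count causes it.

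**Cost.** Minor site paperwork, and notification or submission where local law requires it (section 10.0). No extra visits, procedures or identifiable data are needed. If the change comes after enrolment has begun, the count covers later enrolment only and the sample mixes two recruitment rules, so patients enrolled before and after the change should be identified. The count bounds the bias but does not correct it. If no enrolment remains, item 4 can still be done.

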## **9.8 Other Aspects**

The guidelines for good pharmacoepidemiology practices (GPP) in non-interventional studies will be respected and any applicable local laws and regulations. This trial is not in the scope of Good Clinical Practice (GCP) studies.

## **10.0 Protection of Human Subjects**

This study will be run in compliance with local laws and regulations. Notification/submission to the responsible Ethics Committee, Health Institutions and/or Competent Authorities will be performed as required by local laws and regulations (see Country Information page [Section 12.0]).

Written authorization and/or informed consent will be obtained prior to patient inclusion as requested by local regulations.

## **11.0 Safety Reporting**

### **Product-Related Events Including Adverse Reaction Reporting**

This non-interventional study is not designed to identify or quantify a safety hazard relating to an AbbVie authorized product.

If a patient reports a product-related event (e.g., suspected adverse reaction or product complaint) to his/her healthcare professional during the data collection period or the healthcare professional identifies a product-related event, which is considered related to any AbbVie authorized product, the event should be reported to AbbVie. Any product-related events considered to be related to a non-AbbVie product should be reported in accordance with local laws and regulations to the relevant Regulatory Authority and/or drug marketing authorization holder.

The AbbVie contact details are specified in Country Information page (Section 12.0).

The data on medical history will be collected in a retrospective manner. This retrospective portion of the study is based on secondary use of data previously collected from healthcare professionals for other purposes. Any suspected adverse reactions (adverse events considered to be likely related to an AbbVie product) identified during the course of the retrospective review of data should be reported to AbbVie clearly specifying the suspected adverse reaction was identified during retrospective review in an AbbVie non-interventional study. Any suspected adverse reactions considered to be related to a non-AbbVie product should be reported in accordance with local laws and regulations to the relevant Regulatory Authority and/or drug marketing authorization holder.

## **11.1 Patient Reported Outcomes and/or Quality of Life Questionnaires**

Patient Reported Outcome (PRO) and patient questionnaires data are not considered a potential source of adverse events for the purposes of this study. However, the Health Care Professional (HCP) should review the PRO or questionnaires data. If the HCP identifies a product-related event (such as a suspected adverse reaction), and if determined to be related to an AbbVie authorized product, report to AbbVie.

### **11.1.1 Adverse Reaction Definition**

An adverse reaction is defined as any untoward medical occurrence in a patient, where there is evidence to suggest a causal relationship between the product and the adverse event.

### **11.1.2 Pregnancy Reporting**

In the event of a pregnancy occurrence in a patient or partner taking any AbbVie authorized product during the course of the study, the researcher will report the pregnancy to AbbVie. Any pregnancy in a patient taking a non-AbbVie product should be reported in accordance with local laws and regulations to the relevant Regulatory Authority and/or drug marketing authorization holder.

The AbbVie contact details are specified in Country Information page (Section 12.0).

## **11.2 Product Complaint**

### **11.2.1 Definition**

A Product Complaint is any Complaint related to the biologic or drug component of the product or to the medical device component(s).

For a product this may include, but is not limited to, damaged/broken product or packaging, product appearance whose color/markings do not match the labeling, labeling discrepancies/inadequacies in the labeling/instructions (example: printing illegible), missing components/product, device not working properly, or packaging issues.

For medical devices, a product complaint also includes all deaths of a patient using the device, any illness, injury, or adverse event in the proximity of the device, an adverse event that could be a result of using the device, any event needing medical or surgical intervention including hospitalization while using the device and use errors.

Any information available to help in the determination of causality by the device to the events outlined directly above should be reported.

### **11.2.2 Complaint Reporting**

Product Complaints concerning an AbbVie authorized product and/or device must be reported to AbbVie. The AbbVie contact details are specified in Country Information page (Section 12.0).

Product complaints involving a non-AbbVie product and/or device should be reported to the identified contact or manufacturer, as necessary per local regulations.

Product Complaints may require return of the product with the alleged complaint condition (syringe, pen, etc.) as per standard process.

The description of the complaint is important for AbbVie in order to enable AbbVie to investigate and determine if any corrective actions are required.

## 13.0 Plans for Disseminating and Communicating Study Results

At the end of the study, a report or publication will be written by AbbVie. This report or publication will contain a description of the objectives of the study, the methodology and its results and conclusions. The completed eCRFs, questionnaires and the final study output are the confidential property of AbbVie and may not be released to unauthorized people in any form (publications or presentations) without the express written approval from AbbVie.

## 15.0 Appendices

### Appendix 1: List of copyright protected patient reported outcome questionnaires

- Disease activity measures: DAS28, CDAI, SDAI
- Morning stiffness and joint pain measures
- HAQ-DI
- Functional Assessment of Chronic Illness Therapy (FACIT) Fatigue Scale (Version 4)
- TSQM version 1.4
- WPAI-RA
- SF-36v2
- eHEALS

## Appendix 2: Self – reported adherence

**Put a mark at the line below showing your best guess about how much of your medication you have taken within the last 3 months.**

0% means you have taken no medicine

50% means you have taken half of the prescribed doses

100% means you have taken all prescribed doses

[figure not shown]

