### **9.1.6 Self-Reported Adherence (Appendix 2)**

The terms “adherence” and “compliance” are often used interchangeably, however adherence is becoming the preferred term as it suggests the patient has a less passive role in the management of their medication [34].

In this study a 0-100 mm VAS will be employed to gain numeric insights about patients’ estimation of drug intake adherence.

Visual analog scales (VASs) have been extensively used for assessment in a number of health domains (e.g., acute and chronic pain) and have recently been applied to assessment of antiretroviral therapy medication adherence [74]. It has been shown that patients’ self-evaluation of drug intake evaluated by VAS scores correlates with objective adherence measures and thus can be a valuable, easy to use tool for assessing adherence in IMIDs in routine clinical practice [40, 74, 84].

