#### Comparative subgroup analysis

Subgroup analyses of all measures listed above are planned if there are sufficient patients in each subgroup listed below:

- According to the RA treatment
  - Patients currently treated with any synthetic DMARDs, tsDMARDs, csDMARDs, bDMARDs

- Patients with previous exposure to 1 bDMARD or 2 bDMARD
- Patients treated with orally or parenterally administered DMARD
- Patients treated with IV or SC administered DMARD
- Patients treated with DMARD monotherapy or combination therapy
- According disease activity (high or moderate)
- According to comorbidities
  - Patients with or without any kind of comorbidity
  - Patients with cardiovascular comorbidity

For continuous variables two sample t-tests or non-parametric tests will be used based on the data distribution; for categorical variables appropriate R×C tables will be constructed and Chi-square or exact Fisher tests will be used based on appropriate assumption.

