## Appendix 4: Questionnaire to assess medication preferences

We would like to ask you about your preferences regarding medication used for rheumatoid arthritis. For each questions, please circle one answer which reflect your opinion most likely.

1. What is the referred route of administration?
  - a. Parenteral: Intravenous
  - b. Parenteral: Subcutaneous
  - c. Oral
2. What is the preferred frequency of administration in case of parenteral administration?
  - a. Biweekly
  - b. Monthly
  - c. 3-monthly
  - d. 6-monthly
3. What is the preferred frequency of administration in case of oral administration?
  - a. Twice per day
  - b. Once per day
  - c. Once per week
4. What is the preferred time until the effect of onset?
  - a. Up to 1 week
  - b. Up to 2 weeks
  - c. Up to 1 months
  - d. Up to 3 months
5. What is your preference regarding drug combinations used for your rheumatoid arthritis?
  - a. Drug combination is not preferred.
  - b. Treatment which requires daily combination is acceptable.
  - c. Treatment which requires combination with another drug once a week is acceptable.
6. What is the most acceptable potential side effect of the medication used for rheumatoid arthritis?
  - a. Increased risks for infections
  - b. Allergic reaction
  - c. Deterioration of my laboratory values
  - d. Increased risk for malignancies
  - e. Weight gain
  - f. Hair thinning or loss
  - g. Skin symptoms e.g. injection site reaction, rash
  - h. Effect on fertility
  - i. Increased risk of cardiovascular diseases

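### The single 3-month adherence scale gives no unambiguous answer to a patient whose only DMARD is dosed less often than every 3 months, which may distort the exploratory adherence comparisons by route and class

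*Protocol*

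**What the plan says.** Section 9.1.6 of the protocol sets the measure: "In this study a 0-100 mm VAS will be employed to gain numeric insights". No other adherence item is listed. The form in Appendix 2 asks for a mark "showing your best guess about how much of your medication you have taken within the last 3 months", whatever the drug or route. It has three anchors. The lower one is absolute: "0% means you have taken no medicine". The middle one refers to half of the prescribed doses, and the upper one reads "100% means you have taken all prescribed doses". The text of the form has no response for a patient who had nothing due.

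The selection criteria in Section 9.0 admit patients who are "Currently treated with any kind of approved csDMARDs, tsDMARDs or bDMARDs", with at least 3 months on current therapy and no limit on dosing interval. Long intervals appear in Appendix 4, under the question "What is the preferred frequency of administration in case of parenteral administration", where the options run from biweekly to 6-monthly.

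The adherence score is a secondary variable (Section 9.5.2). Section 9.5.3 plans subgroup analyses of all measures, including by drug class, by oral or parenteral route, and for "Patients treated with IV or SC administered DMARD". It also plans regressions of adherence on patient characteristics. Section 9.7 warns about self-presentation and faulty recall in self-reported adherence and calls subgroup comparisons exploratory. It does not mention dosing interval.

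**The concern.** The anchors use two different yardsticks. The lower end counts medicine taken; the middle and upper points count doses taken out of doses prescribed. The two agree as long as at least one dose was prescribed in the window. When none was, the second yardstick has a zero denominator: the patient took no medicine, and also missed nothing. One fully adherent patient may mark 0 and another 100.

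Whether this can happen depends on the dosing interval, and so on the drug and its route. Any resulting error would not spread evenly over the study population. It would sit in the parenteral group, and within that group in whichever route and class contains the long-interval drug. Enlarging the sample would not remove it. At stake is the reading of the adherence contrasts by route and class, a topic the protocol's own background raises when it cites better adherence with biological than with conventional oral DMARDs.

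**Working it through.** The protocol states no expected value for adherence, so there is no figure of its own to reproduce. The precision figures in Section 9.3 concern TSQM global satisfaction and play no part here.

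**Inputs from the protocol**
- Look-back window: 3 months (Appendix 2).
- Parenteral intervals named: biweekly, monthly, 3-monthly, 6-monthly (Appendix 4, as preference options only).
- Oral frequencies named: at most one week between doses (Appendix 4).

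**Inputs not in the protocol, varied as assumptions**
- q: share of a route or class subgroup whose only DMARD is given 6-monthly, taken as 2% to 40%.
- m: share of those with no dose due who mark 0 instead of 100, taken as 0 to 1.

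**Step 1. Chance that no dose was due.** With one dose every D months and the visit falling uniformly over the interval, P(no dose due) = max(0, 1 − 3/D).

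| Interval D (months) | 1 − 3/D | P(no dose due) |
|---|---|---|
| 0.5 | −5 | 0 |
| 1 | −2 | 0 |
| 3 | 0 | 0 |
| 6 | 0.5 | 0.5 |

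Of the intervals named, only the 6-monthly one produces the problem. A 3-monthly regimen puts about one dose in the window, apart from borderline timing. The value 0.5 depends on even visit timing. Visits are routine follow-ups (Section 9.2), and their timing relative to dosing is unknown. A patient between months 3 and 6 of a first 6-monthly cycle, who already meets the 3-month treatment rule, would always have no dose due.

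**Step 2. Possible shift of a subgroup mean.** Downward shift on the 0–100 scale = 100 × q × 0.5 × m. For example, q = 10% and m = 0.5 gives 100 × 0.10 × 0.5 × 0.5 = 2.5 points.

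| q | m = 0 | m = 0.5 | m = 1 |
|---|---|---|---|
| 2% | 0 | 0.5 | 1.0 |
| 5% | 0 | 1.25 | 2.5 |
| 10% | 0 | 2.5 | 5.0 |
| 20% | 0 | 5.0 | 10.0 |
| 40% | 0 | 10.0 | 20.0 |

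On the oral frequencies named, q is 0 in the oral group, so any shift in the parenteral mean would pass in full into the oral/parenteral difference.

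The table shows what the wording allows. It does not estimate what will happen, because neither q nor m can be taken from the protocol.

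**The case against.** Several stronger readings are tempting, and the protocol does not support them.

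- **That such a patient has no valid answer.** The upper anchor is true for an on-schedule patient with nothing due. Two of the three anchors speak of prescribed doses, which makes 100 the more natural choice. The fault is ambiguity.
- **That 3-monthly dosing is affected too.** Step 1 gives a probability of zero. Nor is it an error that a patient with a single due dose can score only 0 or 100; that is correct for one dose.
- **That affected patients are known to be in the study.** The 6-monthly interval is an answer to a preference question. No section says that an enrolled patient is on such a regimen. The eligibility rule merely leaves room for it.
- **That the comparisons are biased by a stated number of points.** Any figure needs an assumed drug share and an assumed way of answering. If all affected patients mark 100, the mean does not move, although their scores then say nothing about dose-taking. Combination therapy shrinks the group further: the item asks about medication in general, and a second DMARD due in the window removes the conflict.

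It is also fair to say that these analyses are secondary and exploratory, that subgroup tests run only where numbers suffice, and that a sensitivity analysis would usually be left to the SAP. All of this lowers the weight of the point. It does not resolve the conflict between the anchors, which is fixed by the wording in the protocol. The exploratory label also does not tell a reader that this route-dependent artefact could exist.

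**Conclusion.** The point holds in a narrow form and is of low severity. For a patient whose sole DMARD is given less often than every 3 months and who had no dose due, the two end anchors of the only adherence item contradict each other, and nothing on the form resolves it. This may bias the oral/parenteral, IV/SC and drug-class comparisons of adherence. If it does, it would lower adherence in the subgroup holding the long-interval drug.

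The size is unknown. Across the assumed ranges it runs from zero to 20 points. The upper end requires 40% of a subgroup to be on such a drug alone and every patient with no dose due to mark 0. Both extremes rest on assumptions, as does the one-half probability, which needs visits spread evenly over the dosing interval. The primary TSQM endpoint is untouched.

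**What to change.** **If the form can still be changed:** reword Appendix 2 to ask what share of the doses that were due in the last 3 months was taken, and add a box for patients who had no dose due. Leave those patients out of the adherence analyses and report how many there were. The cost is re-translation of the changed wording and a small loss of N. The form is not on the copyright list in Appendix 1.

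**If it cannot** (Section 5.0 puts the end of data collection at 31 May 2019): use the current-treatment data already collected under Section 8.1 to repeat the route and class comparisons of adherence without patients whose only DMARD is given less often than every 3 months. Patients on 3-monthly regimens should stay in. Add a sentence to Section 9.7 naming the mismatch between the look-back window and the dosing interval. The cost is one sensitivity analysis, one sentence and a small loss of N in that analysis.
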